### Intervention

The study will compare outcomes among patients randomly assigned to one of two treatment conditions: (1) MBIC with DEF (MBIC + DEF); or (2) MBIC with standard education (MBIC + SE). All patients enrolled in the Measurement, Education and Tracking in Integrated Care (METRIC) study will receive MBIC. The schedule of enrollment, interventions, and assessments is outlined in Fig. 1, study flow is outlined in Fig. 2, and page listings for all study components can be found in the Standard Protocol Items: Recommendations for Interventional Trials (SPIRIT) Checklist (see Additional file 1).

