#### Randomization

After a patient screens positive for depression with the iPad Depression Screening application, the provider will immediately facilitate an introduction to the DCM for potential enrollment in the study. The DCM will assess for the presence of the nine diagnostic criteria for major depression from the Diagnostic and Statistical Manual of Mental Disorders (DSM-IV) [41] through a clinical interview. Once the depression diagnosis is confirmed, patients will be offered the opportunity to participate in the study, guided through the informed consent process and randomized to one of two treatment groups. A block randomization list that randomizes 150 participants into 75 blocks will be generated through an online randomization website and will be kept in a locked filing cabinet in the DCM’s office. Patients will be assigned to the group that coordinates with their patient enrollment number on the randomization list. One hundred and fifty patients will be randomly assigned to two possible treatment arms: (1) MBIC + DEF; or (2) MBIC + SE. A randomization log will be maintained by the Project Coordinator, which will include treatment assignment, names of participants, and participant identification numbers.

At the baseline visit, the DCM will have the patient complete all study measures and engage the patient during the regular intake process. The DCM will document the patient’s PHQ-9 screening score, the stigma measures, current treatment preferences (pharmacotherapy, counseling), and potential barriers to care in a research database. The DCM will also explain the compensation schedule, which includes payment for completing measures after the education intervention and each follow-up research visit, and schedule the patient’s education visit and first MBIC appointment to take place after the education visit.

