#### Education

Within one week, patients will return to the clinic to complete their education session and study measures with a research assistant – either SE or DEF, depending on the group to which the patient was randomized. Two bilingual research assistants, hired from the school of social work, will be assigned and trained to deliver the different education interventions (one each, without exposure to the other education materials). Patients will be encouraged to bring family members or loved ones to the education session. Each education session will be provided in English or Spanish, depending on patient preference, and will conclude with compensation to the patient upon completion of the study measures.

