### Data analysis

#### Sample size

A total of 150 participants will be randomly assigned to the treatment and control groups. Intervention and control groups, estimated at 56 participants each, are required to have an 80% chance of detecting an effect size of 0.57 (power = 0.80) with a two-sided 5% significance level between the two group on depression scores. The effect size of 0.57 was calculated in a similar multisite randomized controlled trial of depression among women (N = 205) in an OB-GYN clinic with a similarly racially diverse, mixed socioeconomic status population [57]. Assuming an attrition rate of 25%, 70 participants for each group would be needed in the current study, which represents a cautious estimation. A systematic review of interventions to increase recovery from depression in primary care settings found attrition rates at the 12-month follow-up visit to be in the range of 6–18% [58].

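### Allocation is opened at consent, although the arms do not differ until an education visit up to a week later; opening it on arrival would avoid dilution or post-randomization exclusion by no-shows

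*Protocol article*

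**What the plan says.** All references are to the Protocol article.

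- **Time of allocation (Randomization).** After screening and a diagnostic interview, patients are "guided through the informed consent process and randomized to one of two treatment groups". Baseline measures are taken by the care manager, who is also to "schedule the patient’s education visit and first MBIC appointment to take place after the education visit".
- **First arm-specific contact (Education).** "Within one week, patients will return to the clinic to complete their education session and study measures with a research assistant". Two research assistants are used, one per type of education.
- **What differs between arms (Intervention).** "All patients enrolled in the Measurement, Education and Tracking in Integrated Care (METRIC) study will receive MBIC", so the education session is the only planned difference.
- **Analysis set (Analysis).** Each dependent variable is to be analysed by intent-to-treat. The last sentence of the same section describes the data as coming from participants with baseline, post-education and 12-month visits.
- **Missed follow-up (Follow-up visits).** PHQ-9 scores and medication information are taken from the medical record if available.

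The article does not say how randomized patients who miss the education visit are handled, and gives no reason for allocating before that visit.

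**The concern.** Between allocation and the education session the two arms follow the same path, so nothing in the design needs the allocation to be known that early. The cost of early allocation is a group of randomized patients who received neither education.

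If they are analysed, they carry no effect of the education contrast, and the expected difference shrinks in proportion to their share. This applies to outcomes that can be obtained without attendance: PHQ-9 from the record, and engagement if it is counted in all randomized patients. If they are left out, as the closing sentence of Analysis can be read to allow, the analysis is no longer intent-to-treat, and its validity rests on non-attendance being unrelated to arm.

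Non-return is a plausible risk here. The Abstract names early treatment withdrawal as part of the problem, engagement is itself an Aim 1 outcome, and patients already diagnosed and in treatment are excluded.

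**Working it through.** **Inputs from the Protocol article.** Effect size 0.57, two-sided 5% level, 80% power, 56 evaluable per arm, 25% attrition, 70 per arm after attrition (all Sample size); 150 randomized, taken as 75 per arm (Randomization); 2–3 enrolled per week for 24 months (Setting and participants).

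**Assumptions.** The no-show share q is not in the document; 5%, 10% and 20% are used. The effect of 0.57 is taken to hold among attenders. The 25% attrition is taken to fall equally on attenders and no-shows, so that q is also the no-show share among those analysed.

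**Step 1: the plan's own figure.** The plan claims an "80% chance of detecting an effect size of 0.57 (power = 0.80) with a two-sided 5% significance level", with "Intervention and control groups, estimated at 56 participants each". The normal formula gives n = 2(1.960 + 0.842)² / 0.57² = 15.70 / 0.325 = 48.3, so 49 per arm; the t-test version gives 50. The stated 56 is therefore not reproduced at 80% power; it is the number for about 85%. Also, 56 × 1.25 = 70, whereas 56 / (1 − 0.25) = 74.7, or 75 per arm. The 150 randomized matches 75 per arm, so the planned total is sufficient: 75 × 0.75 = 56.25 evaluable per arm, t-test power 0.85 with no no-shows. This is the starting point below.

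**Step 2: three ways of handling no-shows, 150 consents in each.**

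- Allocate at consent, analyse no-shows: 56.25 per arm, effect 0.57(1 − q).
- Allocate at consent, exclude no-shows: 56.25(1 − q) per arm, effect 0.57.
- Allocate on arrival: 75(1 − q) × 0.75 = 56.25(1 − q) per arm, effect 0.57.

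The second and third have the same numbers and hence the same power.

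| q | Effect if no-shows analysed | Power, no-shows analysed | Per arm, allocation on arrival (or exclusion) | Power |
|---|---|---|---|---|
| 0% | 0.570 | 0.85 | 56.3 | 0.85 |
| 5% | 0.542 | 0.81 | 53.4 | 0.83 |
| 10% | 0.513 | 0.77 | 50.6 | 0.81 |
| 20% | 0.456 | 0.67 | 45.0 | 0.76 |

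Analysing no-shows takes power below 0.80 once q passes about 6–7%; with allocation on arrival this happens at about 12%. The reason is that dilution raises the required sample size by 1/(1 − q)², while losing the no-shows before allocation raises it only by 1/(1 − q).

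**Step 3: consents needed to keep 150 randomized on arrival.** 150/(1 − q) = 158, 167 and 188 at 5%, 10% and 20%. Two to three per week for 104 weeks gives 208–312.

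**Step 4: which outcomes are exposed to what.** Knowledge and stigma are measured right after the session and one month after it. A patient who misses the session has no such score, so at these points the result is missing data, not dilution. PHQ-9 can come from the record, so it can be diluted. Engagement depends on its denominator: the Aim 1 text describes those who received the fotonovela and went on to treatment, which would leave no-shows out, while the intent-to-treat statement would keep them in.

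**The case against.** Randomizing at consent is ordinary practice, and intent-to-treat exists to absorb non-receipt. No no-show rate is given, and the return is within a week with payment for completing measures, so the share may be small. This stands: the size is unknown, and only the direction is certain.

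Four stronger readings are tempting, and the document does not support them.

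- *Every Aim 1 and Aim 2 contrast is shrunk.* It is not: post-session knowledge and stigma would be missing, engagement depends on the denominator, and no-shows with no outcome data fall within the 25% attrition.
- *Excluding no-shows destroys the randomized comparison.* Before the session the arms are treated alike, and nothing says that patients are told their arm. Exclusion biases the contrast only if attendance depends on allocation. Under even exclusion the power gain from changing the timing is nil.
- *Engagement power collapses.* Any such figure needs engagement rates for attenders and for no-shows, and the document gives neither. Missing the session does not by itself bar a patient from treatment.
- *The change costs no patients.* With 150 consents and 20% no-shows, power is about 0.76, below the planned 80%; restoring 150 randomized takes more consents.

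It is also fair to say that 0.57 may already reflect non-attendance in the source trial. The document does not say, so its use for attenders is an assumption. Finally, late allocation removes the earliest disengagers from a trial in which engagement is an outcome. That is a real narrowing, although it agrees with the Aim 1 wording on those who received the intervention.

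**Conclusion.** The point holds as a design improvement of moderate and uncertain size, not as an error that invalidates the trial. Allocation precedes the only arm difference by up to a week and a return visit, with no stated reason, and the text leaves open whether no-shows dilute the comparison or are excluded from it. If they are analysed, allocation on arrival gains about 0.02, 0.04 and 0.10 in PHQ-9 power at 5%, 10% and 20% no-shows for the same 150 consents. If they are excluded, the gain is only that no one is excluded after randomization for missing the session. These figures rest on the assumed no-show shares, on 0.57 applying to attenders, and on 25% attrition that is equal in attenders and no-shows. If no-shows are more often lost to follow-up, dilution is smaller.

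**What to change.** Amend Randomization so that consent, eligibility and baseline measures stay at the index visit, and the next allocation is opened only when the patient has arrived for the education visit, immediately before the session. Report consented patients who do not arrive descriptively, with their baseline characteristics. In Analysis, state that all randomized patients are included, so that the closing sentence cannot be read as requiring a post-education visit. Enrollment began in February 2016, so for patients already randomized under the present timing, keep all of them in the analysis and report no-shows by arm.

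The costs are a protocol amendment; scheduling, because both existing research assistants must be available in education slots and the allocation must be accessible there; and inference limited to patients who attend the education visit. Keeping 150 randomized needs about 158–188 consents at 5–20% no-shows, below the 208–312 implied by the stated enrollment rate. No new staff are needed.

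If the amendment is judged too late, the wording change in Analysis and the report of no-shows by arm are still worth making.

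### Allocation is not reliably concealed: the list uses blocks of two and is kept in the office of the depression care manager who decides eligibility

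*Protocol article*

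**What the plan says.** All places are in the protocol article.

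- **List structure** (Randomization): "A block randomization list that randomizes 150 participants into 75 blocks". The same section says "One hundred and fifty patients will be randomly assigned to two possible treatment arms".
- **Equal arms** (Sample size): no ratio is given, but the groups are planned at one size: "Intervention and control groups, estimated at 56 participants each, are required".
- **Custody** (Randomization): the list "will be kept in a locked filing cabinet in the DCM’s office". The Project Coordinator keeps a log of assignments made, which is a separate record.
- **Assignment** (Randomization): "Patients will be assigned to the group that coordinates with their patient enrollment number on the randomization list". Setting and participants adds that enrollment is in order of arrival.
- **Eligibility** (Randomization): "The DCM will assess for the presence of the nine diagnostic criteria for major depression", by clinical interview.
- **Consent** (Randomization): patients are then "guided through the informed consent process and randomized to one of two treatment groups". The sentence is passive and names no actor.
- **Baseline** (Randomization): "At the baseline visit, the DCM will have the patient complete all study measures and engage the patient during the regular intake process". The DCM also records treatment preferences and books the education visit.
- **Education staff** (Education): there are two research assistants, one for each arm.
- **Treatment** (Measurement-based integrated care): the DCM gives brief psychotherapy every 1–4 weeks in both arms.

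**The concern.** Concealment requires that whoever decides on a patient's entry cannot foresee the next arm. Here two stated features work against that. Blocks of two make half the sequence predictable to anyone who knows the preceding assignment. In addition, the sequence itself is stored in the office of the person whose interview determines eligibility.

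Entry leaves room for judgement. A PHQ-9 of 5 or more counts as a positive screen (Universal screening with iPad technology), so the DCM's diagnostic interview does much of the selecting. If the next arm can be foreseen, the diagnosis or the invitation could be handled differently depending on that arm, knowingly or not. If the arm is known when baseline is taken, the knowledge and stigma scores and the recorded preferences could also be affected. Engagement in treatment, knowledge and stigma are between-arm outcomes under Aim 1, and PHQ-9 change is compared between arms under Aim 2. Selection at entry would bear on all of them. The covariate checks planned in the Analysis section can address measured imbalance only in part.

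**Working it through.** **Block size.** Inputs: 150 participants, 75 blocks, 2 arms (Randomization); equal arms (Sample size).

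150 / 75 = 2 per block on average. A block balanced 1:1 between two arms has an even size of at least 2. If the average is 2 and every block is balanced, every block is therefore exactly 2, with one assignment to each arm.

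**Predictability when past assignments and block size are known.** For a balanced block of size 2m:

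- share of assignments that are certain = 1 / (m + 1)
- expected correct guesses per block = m + (2^(2m) / C(2m, m) − 1) / 2

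| Block size | Certain | Expected correct guesses |
|---|---|---|
| 2 (m = 1) | 1/2 = 50% | [1 + (4/2 − 1)/2] / 2 = 1.5/2 = 75.0% |
| 4 (m = 2) | 1/3 = 33.3% | [2 + (16/6 − 1)/2] / 4 = 2.833/4 = 70.8% |
| 6 (m = 3) | 1/4 = 25% | [3 + (64/20 − 1)/2] / 6 = 4.1/6 = 68.3% |

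Enumerating all balanced blocks gives the same figures. For this trial, 0.50 × 150 = 75 assignments are certain, and 0.75 × 150 = 112.5 are expected to be guessed correctly, against 75 by chance. Sizes 4 and 6 are comparators only; the document does not mention them. They show that larger fixed blocks alone help only modestly, so custody matters at least as much as block size.

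**Can the DCM know past arms?** The DCM books the education visit, and each arm has its own research assistant. The booking therefore probably identifies the arm, even if the cabinet is never opened.

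**Possible bias (assumed inputs).** Suppose patients steered towards one arm differ in prognosis by d from those steered towards the other. Let p be the share of predictable slots in each arm and s the share of those that are steered. Then bias in the arm contrast = p × s × d. With p = 0.5 from blocks of two and d = 0.5 SD (assumed):

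- s = 0.20 (assumed): 0.5 × 0.20 × 0.5 = 0.05 SD
- s = 1.00 (every predictable slot): 0.5 × 1.00 × 0.5 = 0.25 SD

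Relative to the planned effect of 0.57 on depression scores, these are 0.05/0.57 = 9% and 0.25/0.57 = 44%. The upper figure is close to a worst case for prediction from past assignments alone. The range does not cover someone reading the list, where every slot would be known.

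**The case against.** **The full protocol is not shown.** An article may leave concealment details to it. That would answer a complaint about silence, but this article states a block structure and a storage place that together work against concealment.

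**75 blocks may be a slip for 75 per arm.** This is possible. The 50% and 75% figures would then fall, but the text would still need correcting and the custody problem would remain.

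**The cabinet is locked.** A reader might infer that the DCM holds the key. The article does not say who does, and it describes no independent key-holder. The DCM's access is plausible but not stated. The DCM's role in consent is likewise an inference from a passive sentence.

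**Steering is constrained.** Screening is universal, the provider makes the introduction at once, and enrollment is in order of arrival. This stands: it leaves only the interview and the invitation or consent step, and it is why 0.25 SD should not be read as an estimate.

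**Stronger readings that the document does not support:**

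- *The baseline PHQ-9 is biased.* Patients complete it on the iPad, and the medical assistant enters the score in the health record, in connection with a screen that precedes the introduction to the DCM. The DCM only documents that screening score. Follow-up PHQ-9 is also self-reported on the iPad.
- *Baseline is taken after randomization.* Only the order of paragraphs suggests this. The schedule and flow figures are not shown, so baseline may already come first.
- *The DCM reads past arms from the log.* The log belongs to the Project Coordinator. The likelier route is booking the visits.
- *Concealment would stop the DCM from working harder with one arm.* Effort after allocation is a matter of blinding. The DCM sees patients repeatedly after the education session and may hear the arm from them.

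**Conclusion.** The point holds as a flaw in the stated procedure. As written, 75 of 150 assignments follow with certainty from the preceding one, and the best guess is right 75% of the time. This rests on balanced blocks, equal arms and knowledge of the earlier assignment. The first two follow from the document's figures; the third is a probable consequence of the booking arrangement. Separately, the sequence is stored in the office of the person who decides eligibility, with no independent safeguard described.

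The consequence is an opening for selection at the interview or invitation step, and for possible influence on the baseline knowledge and stigma measures and treatment preferences. Nothing in the document shows that either has occurred. The size of any bias is unknown: 0.05 to 0.25 SD under an assumed 0.5 SD prognostic difference with 20% to 100% of predictable slots steered. It should be corrected because it touches the randomized comparison itself and the remedy is cheap.

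**What to change.** For all remaining participants:

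1. Move the unused sequence out of the DCM's office, either to the Project Coordinator, who already keeps the log, or into REDCap, which the study already uses.
2. Regenerate the unused part in undisclosed, randomly varying blocks (for example 4 and 6), switching at the end of a complete pair. If 75 blocks was a slip, correct the text as well.
3. Release each assignment only after diagnosis, consent and baseline measures are recorded, and state this order in the protocol. If it is already the practice, only the statement is new.

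Optionally, have the Project Coordinator book the education visit. This limits what the DCM learns about past arms but will not blind the DCM.

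**Cost.** A short amendment and a new list, with no extra staff or patients and no change to either intervention. Each patient may wait briefly for an assignment. If enrollment stops within a block of 6, the arms may differ by up to 3 in total. Trial status gives enrollment from February 2016 to an estimated January 2018 but not the number still to be enrolled, so the gain cannot be quantified, and patients already randomized are not helped.

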#### Education

Within one week, patients will return to the clinic to complete their education session and study measures with a research assistant – either SE or DEF, depending on the group to which the patient was randomized. Two bilingual research assistants, hired from the school of social work, will be assigned and trained to deliver the different education interventions (one each, without exposure to the other education materials). Patients will be encouraged to bring family members or loved ones to the education session. Each education session will be provided in English or Spanish, depending on patient preference, and will conclude with compensation to the patient upon completion of the study measures.

##### Standard education

The research assistant trained in SE will read the patient education materials from the National Institute of Mental Health (NIMH) [42] which includes: What is depression? What causes depression? Signs and symptoms. Who is at risk? Treating and living with depression. The SE materials emphasize the complexity of depression that involves thoughts and feelings, behaviors, and physical symptoms, and issues of co-morbid illness and depression as a biological disease. The SE education materials are printed in English and Spanish. The SE session will last about 20 min.

##### Depression education fotonovela

The research assistant trained in the DEF will read *Secret Feelings* (*Sentimientos Secretos*) with the patient, including the question and answer page at the back of the booklet. The story is presented in both English and Spanish at a 4th-grade reading level. After reading the *fotonovela* together, the patients will be asked if they have any additional questions. The DEF session will last for about 30–45 min.

